#### Care home-level data

The care home manager/nominated staff member will be asked to complete a care home booklet to provide information on the staff and resident profile of the home, and anonymous home-level data relating to hospital admissions, general practitioner (GP) call-outs, mortality rates, and falls in the last 3 months. At baseline, as part of the screening process, anonymous Physical Activity and Mobility in Residential Care Scale (PAM-RC) (Whitney et al. manuscript submitted) and Barthel Index [23] data will also be collected for all residents to establish the profile of PA, participation in activities of daily living/self-care at the level of the care home, and ambulatory capacity.

#### Staff data

At each data collection time point all staff who have face-to-face contact with residents, with the exception of those acting as a nominated consultee, will be asked to provide basic demographic data about themselves and complete a questionnaire regarding their experience of person-centred care provided in the care home (Person-centred Care Assessment Tool (P-CAT)) [24].

#### Resident-level data

Participating residents will be asked to complete questionnaires (via researcher interview) assessing their level of cognitive impairment (six-item Cognitive Impairment Test (6-CIT)) [25], mood (Geriatric Depression Scale (GDS)) [26], perceived health (EuroQol five dimensions (EQ-5D-5 L)) [27], and quality of life (dementia quality of life tool (DEMQoL)) [28]. Proxy completion of the EQ-5D questionnaire by a member of staff who knows the resident well will also be undertaken for all participating residents. Additionally, where residents are unable to answer the questions themselves, proxy completion of the DEMQoL questionnaire will be undertaken. Appropriate staff members will also be asked to complete questionnaires about physical function and mobility (Functional Ambulation Classification (FAC) and Elderly Mobility Scale (EMS])) of resident(s) they know well. Where possible, the same staff member will provide data for a particular resident throughout the study. Any staff member acting as a nominated consultee will not act as a staff proxy informant so that they remain independent of the research.

Residents who give their consent will be asked to wear an ActiGraph wGT3X-BT accelerometer (Actigraph, Pensacola, FL, USA) on the right hip, secured using an elasticated belt, during waking hours over the course of 7 days to record PA through movement counts collected over 60-s epochs. Valid wear time will be defined as ≥8 h 25 min on ≥4 days. For residents who provide valid data, the amount of time spent in various PA categories [29] and in sedentary behaviour will be identified using cut-points applied to the vertical axis accelerometer counts per minute (cpm) (see Table 2). A detailed protocol will be followed for administration of the accelerometers which will take place after the data collection defined above to ensure that accelerometer wear does not interfere with residents’ routine PA levels and influence their questionnaire outcome assessments.

**Table 2 Tab2:** Accelerometer cut-points

Accelerometer counts per minute (cpm)	PA classification	Examples of activities
<100 cpm	Sedentary	Sitting, reclining
100–759 cpm	Low intensity PA	Upper body movements
760–2019 cpm	Light intensity PA	Self care, slow walk
≥2020 cpm	Moderate-vigorous (MV) PA	Walking, sit-stand transfers

*PA* physical activity

Adverse event data will be collected by a researcher on a monthly basis and the best method of collecting service use data will be explored, including data routinely recorded by the care home as well as, where possible, via receipt of hospital attendance data from NHS Digital and relevant Acute Hospital Trusts.

#### Process evaluation

A mixed-method approach will be employed with different stakeholders, at different levels (all homes; all intervention homes; purposive sub-sample of intervention and control homes).

Data will be collected across all 12 trial homes to describe usual care and the contextual factors within and outwith the care home environment that affect resident PA and sedentary time over the period of the trial. Researchers will use a qualitative, trial-specific observational tool at each data collection time point to obtain insights into residents’ PA at different times, in different locations, and in respect of residents with different types of need. They will also complete a chronology of organisational (including staffing) policy and practice changes that have occurred in the 3 months preceding data collection. Qualitative interviews will be conducted with a senior member of staff in each home at the conclusion of the trial by the dedicated process evaluation researcher(s) to explore the value attached to ‘moving more’ and how this may have changed over the period of the research.

Across all intervention homes, data will be collected on the intervention and implementation process by the process evaluation researcher and programme facilitators. This will include audio recordings of the workshops and collection of documentary data relating to the cyclical process of change over time (observation, action planning, and review sheets). Information will be gathered on which residents have been chosen for action and their characteristics; which domains of “moving more” have been targeted and with what effect; and which staff, occupying which roles, are nominated to provide support and encouragement to residents to engage in more PA. Qualitative interviews will be undertaken with the care home’s intervention lead to explore how the intervention is understood, engaged with, and enacted by different stakeholders in the real life context of individual care homes, and examine how both intervention and contextual factors facilitate, delay, or impede change.

Within a sub-sample of two intervention and two control homes, ethnographic observations of levels of movement within public areas will be conducted by the process evaluation researcher(s) alongside informal discussion with residents about their experience of, and attitudes to, ‘moving more’, and interviews with staff generally about the value they attach to PA and practices in relation to it. These data will allow in-depth evaluation of how the intervention enhances attitudes towards and practices relating to PA among staff and residents over the study duration, over and above any changes that may be introduced within the control homes. Within the intervention homes, it will also contribute to understanding whether change occurs in the pattern of PA and sedentary behaviour over time, as well as in the engagement and reach of the intervention to staff and residents.

Within the sub-sample of two intervention homes, data on the theories of change and how these are enacted and impact on the pattern of movement over time will be collected through observation of implementation team meetings, review of documents relating to the service improvement cycle, and interviews with members of care staff, including the intervention lead, over the course of implementation. Since implementation is conceived of as a process and not a one-off event [30], documenting the process as it evolves over time and in relation to contextual factors in the care home is considered necessary. Analysis will be based on the principles of grounded theory [31].

#### Economic evaluation

A within-trial cost effectiveness analysis will be undertaken from the perspective of the NHS and Personal Social Care Sectors. It will compare costs and outcomes over the 9-month follow-up period between each arm. The analysis will use quality-adjusted life years (QALYs) derived from responses to the EQ-5D-5 L and EQ-5D-5 L proxy [32]. Cost estimates will be based on NHS resource use (accident and emergency/unplanned hospital admissions, falls, soft tissue injuries, NHS and non-NHS service use) collected from care notes and via a health economics questionnaire completed by researcher interviews with staff at 3, 6, and 9 months post-randomisation. The resources associated with implementation and delivery of the intervention will be included in the analysis. These will be based on routine data such as administrative records, trial-specific data collected during implementation, and a detailed description of the implementation and development process provided by the researchers involved in intervention implementation. Unit costs for health service resources will be obtained from national sources such as the Personal Social Services Research Unit (PSSRU), the British National Formulary (BNF), and NHS Reference cost database [33]. The non-parametric bootstrap method will be used to produce a within-trial probabilistic sensitivity analysis of the incremental cost effectiveness ratio. Longer term cost effectiveness will be estimated using a decision analytical model. The long-term cost effectiveness modelling will adopt the same perspective as the within-trial analysis and will follow good practice guidelines [34]. A value of information analysis will be undertaken [35].

### Sample size

We aim to recruit 12 residential care homes (six per arm) with an average of 8–12 participating residents per home, based on recruitment in our earlier studies. A formal power calculation is not appropriate in this feasibility trial as effectiveness is not being evaluated. However, this target sample size allows us to maintain sufficient power for an effect size of 0.50 and above across the outcome measures while increasing the Type I error rate from 0.05 to 0.20 (Table 3). Increasing the Type I error rate provides assurance that the intervention is promising and warrants further evaluation given that we are making a preliminary and non-definitive randomised comparison of the intervention with usual care. It is recognised that, with an increased false-positive rate in this feasibility trial, a definitive trial may not show an intervention effect at the care home level; however, sufficient changes at an individual level may be detected which would also be of interest. The results generated from this study will be used to inform the sample size for a definitive trial.

**Table 3 Tab3:** Anticipated power for a range of effect sizes across outcome measures with six clusters per arm, not accounting for losses to follow-up

Effect size	ICC	Power (cluster size = 8)	Power (cluster size = 12)
0.40	0.05	65%	74%
	0.10	59%	65%
0.50	0.05	79%	87%
	0.10	72%	78%
0.60	0.05	89%	94%
	0.10	83%	88%

*ICC* intra-class correlation coefficient (which represents the amount of correlation between observations (residents) within a cluster (care home))

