### Care home randomisation

Care homes will be randomised on a 1:1 basis to the REACH intervention plus usual care or to usual care alone. Due to the small numbers of care homes (trial clusters), stratified randomisation will be implemented to ensure balance between the arms with respect to size of the care home (small/medium ≤40 beds, large >40 beds) and whether or not an activity co-ordinator is in post (characteristics expected to be correlated with intervention implementation and outcome evaluation).

The allocation will be performed centrally by the statistician at the Clinical Trials Research Unit (CTRU) at the University of Leeds using a computer-generated minimisation program with a random element, following recruitment of residents and completion of their baseline assessments. CTRU will provide the random allocation to researchers involved in intervention implementation and adherence monitoring, so that all care home managers can be informed of their care home’s allocation, and arrangements can be put in place for those homes randomised to intervention delivery. Researchers involved in the collection of outcome measures will not be informed of allocation, and efforts will be made to ensure that they remain blind. This will include maintaining separate office locations for ‘blinded’ and ‘unblinded’ researchers and requesting that care homes do not disclose their allocation to these researchers.

Due to the concern that smaller homes may not have enough residents providing baseline data to ensure sufficient outcome data for evaluation (despite initial assessment that there should be 8–12 eligible residents at the care home), homes will only be randomised if there are at least five participating residents providing baseline data.

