#### Preliminary estimate of the effectiveness of the intervention

Through the use of accelerometers we are able to derive several different PA and sedentary behaviour end-points. We will be able to assess the amount of time residents spend sedentary and in low, light, and moderate to vigorous intensity physical activity (MVPA). We can also assess the number of daily bouts (defined as consecutive minutes) of specified lengths spent in these categories. Examples of such end-points include:Percentage of time spent sedentary and in low-intensity categoriesNumber of daily sedentary bouts of >60 minNumber of daily sedentary bouts of >30 minNumber of daily bouts of low intensity >5 minTotal length of time spent sedentary or in low-intensity physical activityThe total time spent achieving any MVPA

For each PA outcome of interest (as detailed above) measured using the accelerometers, point estimates will be calculated by study arm based on cluster-level summaries, together with a range of CIs (95%, 80%, 67%, and 51%) to give a greater indication of the direction and effect size we might expect to see in a large-scale trial. Data will be reported separately at baseline and at each follow-up time point.

Following a review of the summaries for each of the PA outcomes, the most appropriate end-point for future use in the large-scale trial will be selected. This decision will be made on the basis of both the summary data and any emerging evidence on physiological effects (for example, that increasing the number of breaks in sedentary behaviour is more important than reducing the total amount of sedentary behaviour). No information will be provided split by treatment arm at this stage to avoid selection bias. Once this decision has been made we will then summarise these end-points by trial arm.

A preliminary estimation of effectiveness will be carried out using methods appropriate for cluster randomised trials with a small number of clusters [36]. Point estimates of the 9-month outcome in each arm will be used to obtain difference or ratio estimates of the intervention effect depending on the type of outcome chosen. If the distribution of the summary measures in each arm is skewed, a logarithmic transformation will be considered. Cluster-level summaries will be used to obtain an 80% CI for the intervention effect and hypothesis testing will be conducted at the 20% significance level using the *t* test.

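### Table 3 does not use the 10 degrees of freedom of the planned home-level t test, and the sentence claiming sufficient power at 0.50 omits the table's caveat that losses are ignored

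*Protocol article*

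**What the plan says.** The target in the Sample size section is: "We aim to recruit 12 residential care homes (six per arm) with an average of 8–12 participating residents per home". The section calls a formal power calculation inappropriate for a feasibility trial, then says that "this target sample size allows us to maintain sufficient power for an effect size of 0.50 and above across the outcome measures". The claim is made at a false-positive rate relaxed from 5% to 20%, and it points to Table 3 for the figures. Table 3 gives power for effect sizes 0.40, 0.50 and 0.60, ICCs of 0.05 and 0.10, and 8 or 12 residents per home. Its caption describes the figures as power "with six clusters per arm, not accounting for losses to follow-up". No formula is named, and the word sufficient is not defined.

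The section on the preliminary estimate of effectiveness fixes the test. It is a t test on cluster-level summaries at the 20% level, with an 80% confidence interval, chosen as a method suited to few clusters. The time point is 9 months: "Point estimates of the 9-month outcome in each arm will be used to obtain difference or ratio estimates". The outcomes are accelerometer end-points. Under Resident-level data these are derived only for residents with valid data: "Valid wear time will be defined as ≥8 h 25 min on ≥4 days". Under Care home randomisation, "homes will only be randomised if there are at least five participating residents providing baseline data".

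**The concern.** A power figure should describe the test that will be run on the residents who will be analysed. Here it differs on two counts.

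- **Degrees of freedom.** A t test on 12 home summaries has far fewer degrees of freedom than a calculation that takes residents as the unit and only inflates the variance. The protocol acknowledges the small number of clusters when it chooses the analysis, but the power table does not reflect it.
- **Analysed residents.** Table 3 sets the cluster size to the number recruited. The test uses residents who are still in follow-up at 9 months and meet the wear rule. The caption discloses the first omission (losses) but not the degrees of freedom, and the sentence states its conclusion without either limit.

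At stake is how accurately the sensitivity of the preliminary comparison is described. The sample size and the analysis are not in question.

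**Working it through.** **Inputs**

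- 6 homes per arm; m = 8 or 12 residents per home; ICC = 0.05 or 0.10; effect size d = 0.50 (Sample size section, Table 3).
- Type I error 0.20, taken as two-sided because only that reproduces the table.
- Test: t test on home summaries, so df = 12 − 2 = 10 (section on the preliminary estimate of effectiveness).
- Loss at 9 months, including invalid wear: not given, so any value is an assumption.

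**Formulae**

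- Design effect DE = 1 + (m − 1) × ICC
- Effective residents per arm n = 6m / DE
- Non-centrality λ = d × √(n / 2)
- Normal reference: power ≈ Φ(λ − 1.2816)
- Planned test: power from the non-central t on 10 df, critical value 1.372

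**Step 1: reproduce the table.** For d = 0.50, ICC = 0.05, m = 8: DE = 1 + 7 × 0.05 = 1.35; n = 48 / 1.35 = 35.56; λ = 0.50 × √17.78 = 2.108; power = Φ(0.827) = 79.6%, against 79% printed. Over all 12 cells the normal reference is within 0.8 points of the table. A t reference with resident-level df (12m − 2) is within 0.7 points and fits slightly better. A one-sided 20% test gives 89.7/94.2% and 85.0/89.0% at d = 0.50 and does not fit. A t reference on 10 df lies 0.9 to 2.8 points below the table and matches no cell to rounding.

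**Step 2: planned test, complete data, d = 0.50**

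| ICC | m | DE | n per arm | λ | Table 3 | Normal reference | t, 10 df | Table 3 minus 10 df |
|---|---|---|---|---|---|---|---|---|
| 0.05 | 8 | 1.35 | 35.56 | 2.108 | 79% | 79.6% | 77.0% | 2.0 |
| 0.05 | 12 | 1.55 | 46.45 | 2.410 | 87% | 87.0% | 84.8% | 2.2 |
| 0.10 | 8 | 1.70 | 28.24 | 1.879 | 72% | 72.5% | 69.9% | 2.1 |
| 0.10 | 12 | 2.10 | 34.29 | 2.070 | 78% | 78.5% | 75.9% | 2.1 |

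At d = 0.60 the 10-df figures are 87.3/93.1% (ICC 0.05) and 81.0/86.4% (ICC 0.10), against 89/94% and 83/88% printed.

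**Step 3: illustration of loss, d = 0.50, 10 df, equal homes.** Replace m by the number analysed per home. With 25% loss, 8 becomes 6 and 12 becomes 9; with 40% loss, 4.8 and 7.2.

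| Loss (assumed) | ICC 0.05, m = 8 / 12 | ICC 0.10, m = 8 / 12 |
|---|---|---|
| 0% | 77 / 85% | 70 / 76% |
| 25% | 70 / 79% | 65 / 72% |
| 40% | 65 / 75% | 61 / 68% |

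For example, with ICC 0.05 and 6 analysed per home: DE = 1.25; n = 36 / 1.25 = 28.8; λ = 0.50 × √14.4 = 1.897; power 70%.

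Unequal homes would lower these figures further. Homes can be randomised with five residents, below the table's smallest column, but the documents give no distribution of home sizes, so this is not quantified here.

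**The case against.** The case for leaving the text alone has force.

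- **The df effect is small.** It is about 2 points at 0.50, and the same single cell (ICC 0.05, m = 12) stays above 80%. This stands.
- **The caption is open about losses, and the sentence cites the table.** This stands too: the table is not concealing anything. But the caption covers only losses, not degrees of freedom, and the sentence draws a conclusion that the caveat should limit.
- **The protocol disclaims a formal power calculation, and wear and follow-up rates are what the trial is meant to estimate.** That explains why no loss rate was inserted. It does not justify an unqualified claim of sufficient power, and a range could still be shown.
- **Recruitment was running high.** The Trial status section reports 138 residents in 11 homes, about 12.5 per home. A 36% loss from 12.5 leaves 8 (12.5 × 0.64), which is the table's lower column. The lowest illustrative figures start from m = 8 and so describe a less favourable case than recruitment to date suggests.

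Three stronger readings are tempting, and the documents support none of them. First, a reader might infer that the planned analysis has materially less power as an established fact. The large drops depend on assumed losses; only the 2 points follow from the protocol's own inputs. Second, a reader might infer that a null result will be misread and the intervention dropped. Nothing shown says so: the comparison is described as preliminary, several confidence intervals are to be reported, and the progression criteria are in an additional file that is not shown. Third, a reader might infer that the authors used a normal approximation. Resident-level df fit at least as well; one can say only that 10 df was not used. Nor do the corrections create a shortfall against 80%: three of the four printed cells at 0.50 are already below it, and the protocol sets no such threshold.

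**Conclusion.** The point holds as a modest overstatement. Table 3 is a consistent calculation for a different reference distribution from that of the planned test. At effect size 0.50 with complete data the difference is 2.0 to 2.2 points per cell. This part needs only the protocol's own inputs, a two-sided 20% level, equal homes and an unadjusted test.

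The sentence also claims more than the table supports, because it omits the caveat on losses while the effect is tested at 9 months in residents with valid wear. Any appreciable loss lowers power further. How far is unknown: under assumed losses of 25% and 40%, the gap from the printed figures is about 6 to 9 and 10 to 14 points respectively. These are illustrations, not estimates for this trial.

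**What to change.** 1. Recompute Table 3 for the two-sided 20% t test on six versus six home summaries, using the non-central t on 10 degrees of freedom, and name the method in the caption.
2. Add rows for a stated range of analysable residents per home at 9 months (for example 25% and 40% loss), labelled as assumptions.
3. Replace the sentence that claims sufficient power with the restated figures at 0.50. Say in the text that the complete-data figures ignore both attrition and invalid wear.

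The cost is one recalculated table and one rewritten sentence, with slightly less favourable published figures. The sample size and the planned analysis do not change.

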### Analysis

Statistical analysis of the quantitative elements of the trial is the responsibility of the CTRU statistician, and a detailed statistical analysis plan will be written and agreed before data are analysed. No formal interim analyses are planned and final analysis will take place when all available data have been received and the database has been cleaned and locked. Analyses and data summaries will be conducted on an intention-to-treat population, defined as according to randomisation and regardless of non-compliance with the protocol or withdrawal from the study. The focus of analyses will be descriptive statistics and confidence interval (CI) estimation rather than formal hypothesis testing, with the exception of a preliminary estimate of effectiveness.

